### Study endpoints and outcome measures

#### Primary endpoints

a) the number of reported infection episodes in a cluster within a time frame of 100 reporting weeks

b) the number of reported sick leave episodes in a cluster within a time frame of 100 reporting weeks.

#### Outcome measures

The results will be analyzed comparing the control arm to intervention arm 1 and intervention arm 2, respectively.

The means and standard errors of the numbers of illness and absence episodes in each cluster will be calculated. The efficacy of the two intervention modes will be evaluated separately comparing the corresponding values of invention arm 1 and intervention arm 2 to those of the control arm. The setting will also enable comparisons between intervention arms 1 and 2. Classical hypothesis testing, both for parametric and non-parametric setting and adapted for cluster-randomised trials, with plausible assumption about the data will be launched e.g. similar to that described by [14]. Yet, for getting a probabilistic view towards the study parameters for each arm and every cluster in them, we will exploit the Bayesian approach [15]. With defining our current knowledge of the parameters as a priori and merging it with the likelihood of the data, we will obtain the posterior that will enable us to have a broader view on the study parameters, to see the differences of parameters in each arms and clusters, not only with some sharp frequency tests but also with the probability scope, in order to make inferences e.g. about the likelihood of each parameter to exist in any given interval for the whole population. Due to several person-dependent variables influencing especially the number of sick leaves, this comparison will provide the essential result of the study.

Effects of the interventions on the occurrence of respiratory infections and vomiting/diarrhea diseases will be analyzed both separately and together.

This study will evaluate the efficacy of the entire intervention procedure, not only that of hand washing method, albeit that is where the difference between the two intervention groups lie. The presumption is that based on analyzed self-reports concerning own illness control arm, IR0 ≠ intervention arm, IR1~ intervention arm, IR2. In previous studies performed in semi-closed populations the difference has been 10-50%. Here the default value is closer to the lower than the upper margin of the range.

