### Setting, identification of participating clusters and recruitment

Recruitment of participants was targeted to six companies in the Helsinki Region each including an occupational health clinic of their own. The participating companies include two leading retailers in Finland, two banks, a mining and metallurgical technology provider and a stainless steel producer. Only units involved in common office work were included. The premises of all companies were of the same kind including both open-plan offices and personal office rooms to some employees.

Participants were recruited in 21 operationally distinct volunteer groups, later referred to as study clusters, each including at least 50 persons. Operationally distinct means that members in a cluster had a likelihood of meeting other members of the same cluster during the daily working hours and shared certain physical spaces such as working room, toilets and/or refreshment/resting corners. Members of another cluster did not share these things but, in some cases, might be occasionally met, e.g., in a company restaurant.

Information about the purpose of the study and expected consequences of participating in it were given through different channels including posters and hand-outs, informative talks at staff meetings, and on company intranet web pages. Finally, everybody working in an identified cluster was sent an email requesting to answer a questionnaire about transmission risks (see below) and offering the possibility to participate in the study by weekly email reporting. Inclusion criteria were "Volunteers working in defined units". Exclusion criteria were "Persons with open wounds or chronic eczema in hands".

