### Cluster matching and randomization

To minimize the effect of confounding factors the intervention clusters were matched and randomized prior to onset of the interventions. A questionnaire enquiring, among other things, about numbers and ages of children, their possible out-of-home day care, personal properties such as smoking, chronic diseases, and potential differences in contacts to other people during the daily work, was sent by email to all employees of the selected clusters (Additional file 1). An arbitrary virus transmission risk score was calculated for each cluster based on the results of these potential participant questionnaires [12]. First, the occurrence of each risk factor in a given cluster in relation to the frequency of the factor in the entire population interviewed was assessed. Next, these ratios were inter-connected to reveal an arbitrary transmission risk sum score for the cluster using the following formula:

Indicator variables:

x1 school aged or younger children

x2 at least one child under school age attending day care/pre-school classes/weekly club

x3 smoking (0 = if 1 or 2, otherwise > 1, see questionnaire in Appendix 1)

x4 medically diagnosed chronic heart condition, atherosclerosis, asthma or other respiratory disease

x5 mainly use of public transportation for commuting to work

x6 grown-up exposed to children with cold or vomiting/diarrhea disease at work in school, kindergarten, children's club, health care etc.

where s1-s6 denote corresponding unit-wise sums of each indicator, m1-m6 corresponding total sums over all clusters, i.e. border sums describing frequency of a given variable in the complete material and n, number of people in the cluster.

As can be judged from the above, living with pre-school children in day-care was considered the relatively strongest risk factor and the corresponding risk ratio multiplied by two in the formula. The clusters were then divided in groups of three most similar based on the calculated scores, and members of each triplet were randomized in one of the two intervention arms or in the control arm.

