### Intervention arms and arm-specific guidance of hand hygiene and behavioral habits

A total of seven office units (247 reporting persons) belonged to intervention arm 1 (IR1), in which the intervention was based on hand-washing with soap and water. Further seven office units (199 reporting persons) belonged to intervention arm 2 (IR2), the alcohol disinfectant group. The remaining seven units (218 reporting persons) served as a control arm (IR0). The interventions were planned to continue more than 12 months, preferably one and a half year, in order to cover various season-dependent viral epidemics.

Improved hand hygiene was executed with guided hand-washing with soap and water in one intervention arm and with alcohol based hand rubbing disinfectant in the other. Participants in both arms also received identical guidance on and demonstration of how to avoid infections and how to implement contagion stopping habits. The guidance included instructions for proper coughing and sneezing, for avoiding hand shaking when possible, and frequent hand washing in office and at home. The guidance was given personally to all participants by a specifically trained research nurse and each participant also received written instructions for further reference. The participants in the intervention arms received free of charge containers of the relevant soap or disinfectant, respectively, to be used at home. Participants in the intervention arm 2 also received free of charge containers of disinfectant for personal use in the office. Participants in the control arm were advised to act as before regarding hand hygiene. Toilets and other hand washing spots in all participating clusters were equipped with the same soap, Erisan Nonsid Farmos, Finland, for hand washing. The alcohol containing hand rubbing disinfectant used was LV Käsihuuhde Berner, Finland.

The study was started in two steps following the progression of recruitment. The first batch included 12 units including 374 volunteers in total. The units were matched and randomized together to form four triplets. The second step included 9 units with 306 volunteers in total. These were matched and randomized together to form three triplets. The mean participation percentage in work units was 32.4%, which is reasonable given the large intra-class correlation [13] in the cluster expected in the study.

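### Clusters were randomised within seven matched triplets, but the stated primary comparison does not carry the triplets into the tests; adding them is a nearly free gain in precision

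*Protocol article*

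**What the plan says.** Under Cluster matching and randomization, clusters are grouped by a transmission risk score: "The clusters were then divided in groups of three most similar based on the calculated scores, and members of each triplet were randomized" to the three arms. Under Intervention arms and arm-specific guidance of hand hygiene and behavioral habits, this was done in two batches. For the first batch, "The units were matched and randomized together to form four triplets"; for the second, "These were matched and randomized together to form three triplets".

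The primary comparison is described under Outcome measures: "The results will be analyzed comparing the control arm to intervention arm 1 and intervention arm 2, respectively". That section computes means and standard errors of episode numbers by cluster, and it announces "Classical hypothesis testing, both for parametric and non-parametric setting and adapted for cluster-randomised trials", with a cited source as an example, together with a Bayesian analysis. It mentions no triplet, block, pair or batch.

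After randomisation the triplets reappear only under Evaluation of matching and comparability between the arms and, to the same end, under Evaluation of adherence to instructions. Both serve to judge how comparable the clusters are. No hypothesis test is attached to them.

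**The concern.** Matching and within-triplet randomisation remove between-triplet variation from the arm comparison: each arm has one cluster from every triplet, so differences in risk score, batch and start date cancel out of the difference in arm means. A standard error computed from the spread of clusters within arms puts that variation back. The point estimate is unchanged, but the interval is too wide and the test too cautious.

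The trial has seven clusters per arm and no sample size calculation, and it expects an effect nearer the lower end of a 10-50% range. Precision is therefore scarce, and matching was one of the few design steps that could add some. There is reason to expect at least some correlation even if the risk score predicts poorly, because triplets are nested in batch, the batches started at different times, and infections are seasonal.

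**Working it through.** The article gives no sample size, power, significance level or within-triplet correlation, so there is no figure of its own to reproduce.

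**Design count.** (4 + 3) triplets × 3 = 21 clusters, 7 per arm, which agrees with the stated total.

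**Assumptions.** Two-sided 5% level; normally distributed cluster rates with total SD 1; within-triplet correlation r, so that triplets carry variance r and the remainder is 1 − r.

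**Standard error.** The true variance of the difference between two arm means is 2(1 − r)/7. An analysis without triplets estimates 2/7, so it overstates the standard error by 1/√(1 − r): 1.05 at r = 0.1, 1.20 at r = 0.3 and 1.41 at r = 0.5.

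**Degrees of freedom.** Arm only: 21 − 3 = 18, critical value 2.101. Triplet + arm: 21 − 3 − 6 = 12, critical value 2.179.

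**Confidence half-width, triplet model relative to arm-only** = √(1 − r) × 2.179/2.101 = √(1 − r) × 1.037:

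| r | ratio | effect of adding triplet |
|---|---|---|
| 0 | 1.037 | 3.7% wider |
| 0.1 | 0.984 | about 2% narrower |
| 0.3 | 0.868 | 13% narrower |
| 0.5 | 0.733 | 27% narrower |

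Break-even: r = 1 − (2.101/2.179)² ≈ 0.07.

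**Type I error and power** (simulation, 200,000 trials per setting; difference in between-cluster SDs):

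| r | type I error, arm only | type I error, triplet + arm | power at 1 SD, arm only / triplet + arm | power at 1.65 SD, arm only / triplet + arm |
|---|---|---|---|---|
| 0.1 | about 4% | about 5% | 42% / 44% | 84% / 85% |
| 0.3 | about 2.4% | about 5% | 42% / 54% | 87% / 92% |
| 0.5 | about 1% | about 5% | 41% / 68% | 89% / 98% |

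At r = 0 both tests hold 5%.

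**Non-parametric version.** Re-randomising within triplets only the two arms being compared gives 2^7 = 128 allocations, so the smallest two-sided p is 2/128 = 0.0156. Permuting all three labels gives 6^7 = 279,936 allocations, but that reference set is exact only if all three arms are equal. I checked it with intervention arm 1 equal to control and intervention arm 2 shifted by 1 SD (6,000 trials per setting). A nominal 5% three-label test of arm 1 against control rejected in about 2.0%, 2.1% and 1.3% of trials at r = 0.1, 0.3 and 0.5. The two-arm version stayed between 4% and 5%.

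**The case against.** A reader might infer that the plan ignores the matching, so that its standard errors and p-values do not fit the randomisation. The article does not support that. The sentence on the comparison names contrasts and no error term, and a triplet model would answer exactly those contrasts. Endpoints and summaries are at cluster level, so clustering is covered. The test is left open through a cited source that is not shown and may use matching. An article may also leave model terms to a full analysis plan.

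A reader might also infer a risk of false-positive findings. The figures show the opposite: for r of zero or more, the arm-only test keeps its type I error at or below 5%.

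The size is also open to challenge. The article itself calls the risk score arbitrary, and the matching ignored company, so r may be small. Both starts fall in February-March 2009, a modest offset in 16 months. At r = 0.1 the gain is only a 2% narrower interval and one or two points of power.

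All of this stands, and it makes the point one of efficiency. What remains is that the only description of the primary tests omits the groups within which the clusters were randomised, although the article uses those groups to check comparability. Each announced route can be run with or without the triplets and give different answers, so the choice should be stated.

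**Conclusion.** The point holds as a cheap improvement; it is not an essential correction. The stated primary comparison does not bring the seven triplets into the tests. If they are left out, the tests are valid but conservative when r is positive. The cost in interval width runs from negligible at r near 0.1 to substantial at r of 0.3 to 0.5, and below r of about 0.07 the triplet term costs slightly more than it returns. The payoff is asymmetric: at worst an interval 3.7% wider, against 13% to 27% narrower if the matching worked moderately well. The values of r, the 5% two-sided level and normal cluster rates are assumptions, and the power figures apply only at the differences shown.

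**What to change.** State under Outcome measures that the primary analysis of the cluster rates per 100 reporting weeks includes triplet (7 levels) and arm (3 levels), with 12 residual degrees of freedom, and that the contrasts of control with each intervention arm are taken from that model. Batch is nested in triplet and needs no term of its own.

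For the non-parametric version, re-randomise within triplets only the two arms being compared (128 allocations) and note the floor of p = 0.0156. Keep the three-label permutation for a global test that all three arms are equal. The floor would matter if a multiplicity adjustment were adopted: two primary endpoints by two contrasts under Bonferroni gives 0.05/4 = 0.0125, which the two-arm permutation test could never reach. The article states no such adjustment, so this is only a caution, and a reason to make the model the lead analysis.

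The cost is a change of wording and six residual degrees of freedom (18 to 12). No design or data collection changes.

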### Secondary end points and outcome measures

a) the number of days with reported symptoms of RTI and/or GTI in a cluster within a time frame of 100 reporting weeks

b) the number of days-off due to own RTI or GTI in a cluster within a time frame of 100 reporting weeks

Evaluation of significance and presumptions will be the same as in primary outcome measures. As the implemented intervention presumably affects the probability to fall ill on the first hand and not so much on the duration of the illness, the potential differences in this comparison may be smaller than when using the primary end points

### Other analyses

#### Overall impact of infectious diseases on work contribution and the modulating efficacy of the interventions

In addition to the aspects in the primary and secondary outcome measures this will include absences due to RTI or GTI of dependant. Analyses similar to those described above for *periods of sick leaves *will be carried out using the *periods of absence *as starting point.

#### Transmission routes

Suspected origin of contagion will be analyzed by connecting the exposure recognized by the reporting person during the same or preceding week of the onset of an infection period (1) at work, (2) on business travel, (3) at home or (4) elsewhere during free time. Detailed definitions for this analysis will be created later.

#### Epidemiological research topics

The following analyses for "episodes" will all be carried out for the different infection and sick leave episodes. Detailed definitions needed for the analysis will be created later.

1) Seasonal variation of the episodes and their connection to the occurrence of infectious agents in the participating companies and, on the other hand, in Finnish population in general also utilizing molecular epidemiology of the infectious agents.

2) Distributions of the incidence and duration of episodes per person (0, 1, 2 etc episodes per person-year in relation to selected information derived from the transmission risk survey.

3) Temporal connection of the distinct episodes to each other within the clusters (optional).

## Discussion

### Potential limitations and emerged complications of the study

As mentioned in the introduction, the end-points of this trial, frequency of infectious disease episodes in office employees and that of the consequent periods of days off from work are influenced by a multitude of person-dependent and environmental factors. For some of the confounding factors attempts can be made to eliminate them or at least to minimize their effect while others cannot be regulated. Launching of the present intervention trial among the office staff of various commercial companies was coinciding with the international economical recession resulting in staff reorganization programs in some of the companies, which somewhat delayed and complicated our cluster definitions. A major challenge for the trial setup emerged after onset of the interventions, the influenza A/H1N1 pandemic that reached Finland in summer 2009 and prompted widely publicized improved hand hygiene campaigns at the national level, partly further detailed by the occupational health care units of the participating companies. Obviously, this influenced the behavior of the study participants in the control arm as well, even though it did not influence the participation percentage in the units. Some of the resulting compromises are discussed in the following.

### Lack of sample size calculations and power estimates

Although previous studies on the effects of improved hand hygiene on the occurrence of RTI and GTI appear to yield positive results in semi-closed populations, the results have been variable. We also considered that in the office work setup reintroduction of infections from outside the cluster would have a relatively greater influence than e.g. in a hospital ward. Hence, improved hygiene on the premises might have relatively less impact on the overall transmission of infections. We decided to extend the recommendation of exploiting improved hygiene at home as well, but obviously that is even more difficult to control than that in office. Therefore, we decided that sample size calculation was not possible in the lack of reliable basis for the necessary assumptions.

On the other hand, it was clear that this kind of intervention could not be randomized as an individual case-control study as cluster effects on the end points are obvious ranging from contagion at work to working team dependent traditions of symptom severity necessary to stay home. In matching the clusters we ignored, however, the company, but gave value to potential sources of contagion at home and in leisure time. We could not find any tools for determining the optimal size of a cluster. For statistical analysis in cluster randomized trials the number of people in a cluster is sometimes considered to be negatively correlated for the capacity to detect differences. On the other hand, a certain number of susceptible individuals are required for a virus to be able to circulate in a host population. We chose an arbitrary lower limit of 50 people in our study clusters. It is clear that we should have been able to recruit a larger number of clusters but because of the required operational unity and independence of distinct clusters we could not offer the recruitment to the entire staff in the dedicated companies (about 10000).

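### Triplets were matched on a score from surveys sent to all staff, but about a third of staff report, and the primary comparison states no adjustment for reporters' own day-care exposure

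*Protocol article*

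**What the plan says.** Under Cluster matching and randomization, the risk questionnaire "was sent by email to all employees of the selected clusters". The matching score was computed per cluster "based on the results of these potential participant questionnaires". Within the score, "living with pre-school children in day-care was considered the relatively strongest risk factor", and its ratio was doubled.

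Under Intervention arms, the article reports: "The mean participation percentage in work units was 32.4%, which is reasonable given the large intra-class correlation".

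Under Lack of sample size calculations, company was deliberately left out: "In matching the clusters we ignored, however, the company, but gave value to potential sources of contagion at home and in leisure time". The sentence before it names "working team dependent traditions of symptom severity necessary to stay home" among the cluster effects on the endpoints.

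Under Outcome measures, the primary comparison rests on means and standard errors of episode counts per cluster, with tests adapted to cluster randomisation and a Bayesian analysis. No covariate is named. The section on matching and comparability plans to repeat the risk survey at the end, count drop-outs and recruits, and compare hygiene-survey results. It does not say what follows if the arms differ. Under Epidemiological research topics, episodes per person are to be related to risk-survey information, so survey answers appear linkable to reporters.

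**The concern.** Matching helps only to the extent that the matched characteristic describes the people whose outcomes are compared. Here the score describes those who answered a survey sent to whole units, while outcomes come from a volunteer minority. If volunteers differ from their unit in day-care exposure, and differ by varying amounts across units, two clusters with similar scores can have unlike reporters.

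The intra-class correlation does not answer this. The variance of a cluster mean is proportional to ICC + (1 - ICC)/m, so when the ICC is large, little precision is lost by having few reporters (m). That is an argument about how many people report. It says nothing about which people report.

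With seven clusters per arm and an expected effect near the lower end of 10-50%, leaving the factor that the plan itself ranks highest unadjusted adds avoidable noise to the primary result.

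**Working it through.** **Inputs from the article.** Reporters per arm are 247, 199 and 218. Volunteers by step are 374 and 306. There are 12 + 9 = 21 clusters in 4 + 3 = 7 triplets, six companies, and mean participation of 32.4%.

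**The plan's own figure.** Staff numbers per unit are not given, so 32.4% cannot be reproduced. It can be checked for plausibility, treating the unit mean as a pooled share:
- Reporters: 247 + 199 + 218 = 664, and 664/21 = 31.6 per cluster. Volunteers: 374 + 306 = 680, and 680/21 = 32.4 per cluster.
- Implied staff: 664/0.324 = 2,049, or 98 per cluster; 680/0.324 = 2,099, or 100 per cluster. Both are consistent with the minimum of 50.

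**Day-care imbalance if reporters are a random subset of their unit.** Assumptions: day-care share p of 10-30%, rate ratio RR of 1.25-2, m = 32 reporters out of N = 99.
- SD of the reporter share around the unit share = sqrt[p(1 - p)/m x (N - m)/(N - 1)]. For p = 0.2: sqrt(0.16/32 x 67/98) = 0.058. For p = 0.1 and 0.3: 0.044 and 0.067.
- SD of the difference between two arms of seven clusters = that value x sqrt(2/7): 0.023, 0.031 and 0.036 for p = 0.1, 0.2 and 0.3.
- SD of the relative shift in the arm ratio = arm SD x (RR - 1)/(1 + p(RR - 1)).

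| p | RR 1.25 | RR 1.5 | RR 2 |
|---|---|---|---|
| 0.1 | 0.6% | 1.1% | 2.1% |
| 0.2 | 0.7% | 1.4% | 2.6% |
| 0.3 | 0.8% | 1.6% | 2.8% |

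This counts only the departure of reporters from their own unit. It does not count imperfect matching on a composite score.

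**If the arms' reporters differ by a given gap** (base share 20%), shift = (1 + (0.2 + gap)(RR - 1))/(1 + 0.2(RR - 1)) - 1:
- Gap of 10 points: 1.075/1.05 - 1 = 2.4% at RR 1.25; 1.3/1.2 - 1 = 8.3% at RR 2.
- Gap of 20 points: 4.8% to 16.7%.

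A 10-point gap is about three to four of the arm SDs above (0.10/0.036 = 2.8; 0.10/0.023 = 4.3). It would need selective volunteering, not random participation.

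**What adjustment for day care does.** Day-care status varies between people within a cluster, so its coefficient comes largely from within-cluster contrasts and takes up little of the arm effect. In a simulation on assumed inputs, the two-stage estimate was 0.102 against 0.103 unadjusted, with standard error 0.116 against 0.119 (0.116/0.119 = 0.975, about 2.5% smaller). No cluster-level degrees of freedom are used.

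**What company would do in the same first stage.** Company is constant within a cluster, so six companies take 5 of the 20 between-cluster degrees of freedom. A randomised arm contrast lies on average 5/20 = 25% in that space, and a first stage without arm removes that part. A simulation agrees: 21 clusters in 7 triplets, company sizes 4,4,4,3,3,3 or 7,5,3,2,2,2 assigned independently of triplet, between-cluster SD 0.2 (all assumed), 8,000 draws. A true log effect of 0.100 came out at 0.074-0.076, against 0.099-0.102 unadjusted.

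Fitted jointly with arm as fixed terms, company cuts the residual degrees of freedom of a triplet-and-arm model from 21 - 1 - 6 - 2 = 12 to 7. In a matched-pair comparison it cuts them from 6 to 1, and the 97.5% t quantile rises from 2.45 to 12.7.

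**The case against.** The other side has five points.

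- **Silence is not refusal.** The test and the Bayesian model are left open, covariates are usually fixed in an analysis plan that is not shown, and comparability checks are planned. This stands: the article states no adjustment, which is weaker than ruling one out. What is stated, and does not hold, is the appeal to the intra-class correlation.
- **Respondents and reporters may overlap heavily.** One email carried both the survey and the invitation, and the survey response rate is not given. For a contagious outcome, the risk profile of everyone sharing the space is also a reasonable thing to match on. This stands too, so a mismatch is possible but not shown.
- **Randomisation covers chance imbalance.** Correct for the initial volunteers, who came forward before arms were designated. It covers recruits and arm-changers after onset less well, because joining could then depend on arm.
- **A reader might infer that company belongs in the primary model**, at no cost in degrees of freedom and with an 11-37% cut in the standard error (1 - sqrt(1 - f), if company explained f = 20-60% of between-cluster variance). The documents give no such share, and the working shows that the cost is real. The traditions the article mentions belong to working teams, that is, to the clusters already randomised, and they concern staying home, so they bear on sick leave more than on infection episodes.
- **A reader might cite the differing absence records between companies.** Those are official records, which the article says it replaced with standard self-reporting. They do not support the point.

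**Conclusion.** The point holds in a limited form. The score used for matching may not describe the reporters, the reason given for accepting 32.4% participation does not address that, and the stated primary comparison has no adjustment for the risk factor the plan weights most.

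The expected gain is small to moderate. Under random participation the arm ratio moves with an SD of about 0.6-2.8%, and by several per cent more if volunteering differs between arms. Day-care shares and rate ratios are assumptions; the article gives neither. The issue is precision and chance imbalance. A reader might infer that the trial is systematically biased, but random allocation does not support that, with the possible exception of people who joined or moved after onset. Leaving company out of matching was openly disclosed. It justifies a table and a sensitivity analysis, not a term in the primary model.

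**What to change.** Prespecify a two-stage primary analysis for both primary endpoints, before the analysis planned to start in June 2010.

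1. **Stage 1.** Individual-level Poisson model of episodes with log reporting weeks as offset, own child in day care (x2, with a 'missing' category) and calendar month, arm omitted. Sum the fitted values to expected episodes per cluster. Do not include company here.
2. **Stage 2.** Compare log(observed/expected) by arm within triplets, each intervention arm against control.
3. Report the unadjusted result alongside.
4. Tabulate by triplet and arm the risk score recomputed on enrolled participants, and company.
5. Examine company only in a sensitivity analysis that fits it jointly with arm, for example as a random effect.
6. Replace the intra-class-correlation justification with a statement that participation may be selective, and refer to the table.

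The cost is analysis wording and a linkage step; no new data are needed. The downside is incomplete linkage: the article does not show that every reporter answered the survey. Later recruits may be covered only by the end-of-trial repeat, which falls after allocation. The number in the 'missing' category should be reported by arm.
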